### **5. ETHICAL CONSIDERATIONS**

The two study drugs which are compared in this trial have good safety profiles, are widely used and result in very few adverse events. All children enrolled in the study will benefit from treatment. All diagnosed parasitic infections will be treated according to national guidelines of Lao PDR.

The study aim and procedures will be explained to village and school authorities and health staff and their agreement obtained. Authorization to conduct the study will be obtained from the provincial and district health and education authorities. Furthermore, informed oral consent will be obtained from the provincial and district education departments as well as from the head teachers of the schools.

The study aims and procedures and benefits and possible adverse effects described to all children in Lao language before enrollment. Children can withdraw at any time. The day before the study the parents and/or legal guardians of participating children will be informed and signed the informed consent form.

Ethical approval for this study will be obtained from the Lao National Ethics Committee for Health Research (NECHR), Vientiane, and Ethical Committee of Canton of Basel-Stadt and Baselland (EKBB), Basel, Switzerland.

#### **I.2 Departure to the field on 21st April 2008**

- i. Meet the provincial and district health officers in Champasack province
- ii. Meet the director of the provincial malaria station to obtain the microscopes and recruit the technical staffs.
- iii. Establish team work and plan next step.

#### **I.3 Field collection data**

##### **On the first day:**

- i. Meet the head of school and obtain the list of the schoolchildren and prepare line listing (the line listings are very important to track of the enrolled subjects)
- ii. Meet the parents or legal guardians and children in order to receive all the procedures and the information before enrollment
- iii. Distribute informed consent form and the first stool container with clear instruction on how provide a fresh stool sample to schoolchildren with support of teachers
- iv. Organize team work for following work days.

##### **On the Second day:**

- i. Register and collect stool samples using X mark on the stool samples in the school Line Listing
- ii. Distribute the second stool container
- iii. Check for missing stool samples

##### **On the Third day**

- i. Check and collect the missing second stool samples
- ii. Distribute the second stool samples
- iii. Check for missing stool samples
- iv. Prepare for administration of drugs

##### **On the fourth day**

- i. A random selection of subjects infected with hookworm infection into two equal arms performed by a research coordinator.
- ii. Administration of albendazole and mebendazole in each group
- iii. Treatment will be observed and elicit adverse effects at 24 h

**II. Follow up at day 21-23 (from 20th to 23rd May 2008 of treatment in hookworm infection.**

- i. Repeat base-line measurement (except hemoglobin concentration)
- ii. Treatment will be given to those with infections.

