#### 4.3 Primary outcome measures

1. Hookworm parasite clearance (no egg excretion of initially hookworm-positive children after treatment), assessed 21-23 days post-treatment.
2. Hookworm egg reduction rate (reduction of hookworm intensity, measured in epg) 21-23 days post-treatment.

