#### 4.5 Time schedule

1. Baseline screening (from 28nd to 4th May 2008): From each child two stool samples will be collected within 2-3 days and examined with the Kato-Katz method (Katz et al., 1972). Two Kato-Katz thick smears will be prepared from each stool sample. Hookworm-positive children (at least 1 hookworm egg in one of the four Kato-Katz thick smears) will be treated.

2. End-of-study screening (from 27th to 30th May 2008; 21-23 days post-treatment): From each child, 2 stool samples will be obtained within 2-3 days and duplicate Kato-Katz thick smears will be examined as before.

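### Section 4.5 and Appendix 1 give non-overlapping calendar dates for the only primary-outcome visit, both labelled 21-23 days after treatment, and no single treatment date fits both

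*Protocol*

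**What the plan says.** Section 4.3 ties both primary outcomes to the same interval: "Hookworm parasite clearance (no egg excretion of initially hookworm-positive children after treatment), assessed 21-23 days post-treatment" and "Hookworm egg reduction rate (reduction of hookworm intensity, measured in epg) 21-23 days post-treatment". The same interval from treatment is given in Sections 4.5, 4.6, 4.8 and 4.8.3 and in Appendix 1, part II.

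Two places turn that interval into calendar dates:

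- Section 4.5: "End-of-study screening (from 27 th to 30 th May 2008; 21-23 days post-treatment".
- Appendix 1, part II: "Follow up at day 21-23 (from 20 th to 23 rd May 2008".

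The start of the clock is less clear. Section 4.5 gives "Baseline screening (from 28 nd to 4 th May 2008", with no month printed for the start. Appendix 1, part I.2, gives "Departure to the field on 21 st April 2008". Appendix 1, part I.3, lists "Administration of albendazole and mebendazole in each group" under the fourth field day, without a calendar date. Sections 4.4 and 4.8 describe one primary school.

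**The concern.** Two current parts of the protocol give different weeks for the same visit, and each claims to be 21-23 days after dosing. Appendix 1 is the step-by-step instruction for the field team, so its dates may be the ones used to book staff and collect stools.

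The visit matters because it is the only post-treatment stool assessment, and both primary outcomes come from it. A mistimed visit cannot simply be repeated: Appendix 1, part II, has infected children treated at follow-up, and Section 4.8.3 has them treated at the end of the trial. After that treatment, a later stool no longer measures the response to the randomised drug.

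**Working it through.** **Inputs.** Outcome interval: days 21 to 23 after treatment (Section 4.3). Appendix dates: 20-23 May 2008 (Appendix 1, part II). Section 4.5 dates: 27-30 May 2008. Treatment: the fourth field day, undated (Appendix 1, part I.3). Screening: from the 28th, month not printed, to 4 May (Section 4.5).

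**Step 1: can one treatment date serve both sets?** For a given treatment date, any two visit dates inside days 21-23 differ by at most 23 − 21 = 2 days. The closest dates in the two sets are 23 May and 27 May, which differ by 4 days. Since 4 > 2, no treatment date puts even one day of each set inside the interval. For any single treatment date, at least one set lies wholly outside it.

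**Step 2: what dosing does each set imply?** Subtract 21 days from the first date and 23 days from the last.

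- Appendix: 20 May − 21 = 29 April; 23 May − 23 = 30 April.
- Section 4.5: 27 May − 21 = 6 May; 30 May − 23 = 7 May.

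The implied dosing dates are seven days apart.

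**Step 3: elapsed days for candidate treatment dates** (visit date minus treatment date).

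| Treatment date | 20-23 May (Appendix 1) | 27-30 May (Section 4.5) |
|---|---|---|
| 29 April | days 21-24 | days 28-31 |
| 30 April | days 20-23 | days 27-30 |
| 1 May | days 19-22 | days 26-29 |
| 3 May | days 17-20 | days 24-27 |
| 4 May | days 16-19 | days 23-26 |
| 5 May | days 15-18 | days 22-25 |
| 6 May | days 14-17 | days 21-24 |
| 7 May | days 13-16 | days 20-23 |

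Two rows follow from readings of the protocol. If the 28th means 28 April and that is field day one, the fourth day is 1 May (28, 29, 30 April, 1 May). If dosing waits until screening has closed on 4 May, the first possible day is 5 May. Neither reading is stated, and the departure on 21 April does not date field day one. The other rows show how the answer moves with the assumption. With dosing on 3 May, neither set contains a valid day.

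**Step 4: direction.** With dosing on 4 May or later, every appendix date is at day 19 or earlier, which is wholly too early. With dosing on 29-30 April, every Section 4.5 date is at day 27 or later, which is wholly too late.

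**The case against.** The strongest reply is that the outcome definition is not in conflict. The interval from treatment is the same throughout, and even the appendix line with the differing dates carries the day 21-23 label. A team that counts from the real dosing day stays within the definition whichever dates are printed. This stands, and it limits the point: a reader might infer that the protocol defines its endpoint in two ways, but only the calendar dates disagree. It does not remove the point, because the protocol prints no treatment date and does not say whether the day count or the printed date prevails.

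A second reply is that both arms are treated in one school on the same listed field day, so a mistimed visit shifts both together. This also stands. A reader might infer a biased comparison of the two drugs, but the documents hold nothing that would show or quantify one.

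Third, each printed set covers four days against a three-day interval, which might look like another error. It need not be one: dosing on two consecutive days gives combined windows of exactly four dates (29 April covers 20-22 May and 30 April covers 21-23 May; likewise 6 and 7 May for 27-30 May). Appendix 1 lists dosing under one day, but the span alone proves nothing.

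Finally, two groups of children dosed a week apart would make both sets correct. The protocol describes no such arrangement; it has one school and one treatment day.

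**Conclusion.** The contradiction is real and follows from the printed dates alone: the sets do not overlap, and no single treatment date satisfies both. At least one set would put some or all samples from the only primary-outcome visit outside the protocol's own interval, so the cure and egg reduction rates would not be measured as defined.

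The size is conditional. Dosing on 1 May gives days 19-22 and 26-29; dosing on 5 May gives days 15-18 and 22-25. In those two cases the worst departures are 21 − 15 = 6 days early and 29 − 23 = 6 days late. A reader might take six days as a limit, but it is not one: dosing on 7 May puts the first appendix date at day 13 (8 days early), and dosing on 29 April puts the last Section 4.5 date at day 31 (8 days late). The documents do not show which set was intended. This is a date inconsistency to settle before fieldwork, not a flaw in the design or a demonstrated bias between the drugs.

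**What to change.** Reconcile Section 4.5, the fourth-day entry in Appendix 1, part I.3, and Appendix 1, part II, so that they give one stated treatment date and one follow-up window, and print the missing month for the start of screening. Add a sentence saying that the existing 21-23 day rule, counted from each child's recorded treatment date, prevails over any printed calendar date. Record the actual collection date of each follow-up stool, so that samples outside the interval can be identified.

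The cost is a few edited lines and a date entry on the stool record form. Sample size, visits and laboratory work do not change.

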**III. Measurement instruments**

- a. Lao consent form
- b. Line listing schoolchildren
- c. Individual questionnaire
- d. Kato-Katz record form
- e. Side effect form
- f. Treatment form
